### ***1.2 Eligibility for the survey***

For the prevalence survey all 16 clusters were mapped using OpenStreetMap and the road networks were divided into sections of approximately 200 metres in length. Sections were each allocated an ID number, and simple random sampling was used to select 40 street sections and a backup list of 40 extra sections, in each cluster. The list of selected street sections was sent to the study coordinator. The study coordinator arranged for the survey team to survey all selected street sections. If the first list was completed before 700 participants had been enrolled, the team moved on to the backup list.

The entire survey aimed to enrol 700 participants per cluster, to meet the requirements of the CHIEDZA trial. The sample size for STICH is 300 per cluster. Therefore, data collection days of the survey were randomly allocated to STICH or non-STICH, stratified by weekday/Saturday, with 55% of days allocated to STICH. All participants recruited on STICH days were asked to provide a urine sample which will be tested for 5 STIs using Seegene (Allplex™ STI Essential Assay). Vaginal swab samples were not used in the prevalence survey. The 5 STIs are *C. trachomatis*, *N. gonorrhoeae*, *T. vaginalis*, *Ureaplasma urealyticum* and *Mycoplasma genitalium*. 55% of days were allocated to STICH because it was estimated that data collection would be slower on STICH days (due to the urine sampling) and so 55% of days are required to obtain 43% (300/700) of the participants.

Data collectors visited every dwelling in the allocated street sections and enumerated household members. If any household members were aged 18-24 years, they approached these potential participants for consent. If eligible participants were not at home the data collectors made up to 3 return visits on three different days.

Household members aged 18-24 were shown a video which explains the survey procedures and gave consent if they agreed to participate. The video includes details of STICH including the need for a urine sample and the tests to be performed. Paper consent forms were used in case of video failure, and for a small number of participants as a control group for a randomised controlled trial of consent methods.

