## • Executive Summary

Young people fare disproportionately poorly across the HIV care continuum compared to other age-groups; the prevalence of undiagnosed HIV is substantially higher, and coverage of and adherence to antiretroviral therapy is lower, resulting overall in worse virological outcomes.

**Aim:** The aim is to determine the impact of an integrated community-based package of HIV services incorporating HIV testing, linkage to care and ongoing adherence support, combined with sexual and reproductive health services and general health counselling for 16 to 24 year olds on population level HIV viral load in a high HIV prevalence setting.

**Design:** This is a two-arm cluster-randomised trial in 24 clusters randomised 1:1 to standard of care or to the intervention package.

**Intervention:** Community-based package of services that includes: HIV testing and counselling, delivery of antiretroviral therapy, adherence support groups, mHealth, condoms, menstrual hygiene management, contraception and treatment of sexually transmitted infections, referral for voluntary medical male circumcision, risk reduction counselling and general health information and counselling. The intervention will be implemented over a 30 month period (a six month extension over the originally planned 24 months to mitigate against the effects of lockdowns due to the COVID19 pandemic. The intervention will be implemented in 12 clusters, each with a population of approximately 2500 16-24 year olds.

**Study Outcomes:** The study outcomes will be determined at a population level through a community cross-sectional survey among 18 to 24 year olds two years following the implementation of the intervention. The primary outcome is the proportion with HIV with a viral load <1000 copies/ml. The secondary outcomes will reflect each step of the HIV care cascade: proportion with HIV who know their HIV status, proportion of those who know their HIV-positive status who are currently taking antiretroviral therapy, proportion of those taking antiretroviral therapy who are virally suppressed. Sexual and reproductive health knowledge, and other health risks and behaviour will also be assessed. In addition a random sample of 300 per cluster will be surveyed to investigate the effect of providing unselected STI testing on prevalence of STIs.

**Study population:** The end-line survey will recruit 700 18-24 year olds per cluster (total 16,800).

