### ***d. 2.3 Study design***

A cluster randomised trial design will be used to address the objectives of the study. The study will be conducted in three provinces of Zimbabwe (Harare, Bulawayo and Mashonaland East). A total of 24 study clusters, stratified by province, will be randomised in a 1:1 allocation ratio to one of the following two arms:

- i. Control Arm - Existing HIV and SRH services
- ii. Intervention Arm - Community-based intervention

The target population for the intervention will be individuals aged 16-24 years. In Zimbabwe, individuals aged 16 years and older are able to access SRH and HIV services without guardian consent.

The definition of a cluster, cluster selection and the randomisation method are described in Section 4.2. A pilot will be conducted to test the relevance, acceptability and feasibility of the intervention components, and to optimise trial procedures. The pilot will be delivered over a three-month period in one of the trial clusters in Harare. Iterative loops of evaluation will be used to refine the intervention procedures during the pilot phase.

The intervention will be implemented over a 30 month period in each cluster. This is an extension of six months beyond the originally planned 24 months to mitigate against the effects of the COVID19-related lockdowns during which service provision was not feasible. At the end of this period, a population cross-sectional survey will be conducted to ascertain outcomes. The deployment of the intervention will occur in phases with 4 clusters implementing the intervention first, followed by the next 4 clusters 3 months later and the final 4 clusters starting a further 3 months later. The intervention will be implemented in phases to ensure that the final survey is completed within three months of the end of the intervention.

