### **iv. 3.2.4 SRH and HIV prevention**

Safe and easily accessible services will be identified in each of the study clusters and expedited referral will be arranged for youth requesting VMMC.

Syndromic management of STIs based on national guidelines will be provided. Syndromic management has been standard of care in many LMICs due to the resource constraints for laboratory testing for STIs including lack of adequately trained personnel, laboratory infrastructure and robust quality control. The main limitation of the syndromic management approach is that individuals with asymptomatic STIs (the majority) are not identified. The prevalence of STIs in

southern Africa is high among youth and untreated STIs result in considerable morbidity, and at a public health level, STIs facilitate HIV transmission.

In recent years, near point of care tests of STIs have been developed, including a test for GC and CT that utilises the closed GeneXpert system. The GeneXpert platform was first introduced for TB diagnostics and is widely available. The test is performed on a urine sample with minimal processing required. In addition, a lateral flow assay for *Trichomonas vaginalis*, is a point of care test that is performed on self-taken vaginal swabs. CHIEDZA will offer testing for GC and CT (male and female clients) and for TV (females only), contingent upon availability of test kits.

Other services include advice and information on MHM and provision of MHM products (e.g. menstrual cup, reusable pads and disposable pads and analgesia - see details of the MHM services provided in Section 5.4.3), condoms, pregnancy testing, contraception including LARCs (emergency contraception, depot injections, implants, Intra-uterine contraceptive devices (IUCDs), and the oral contraceptive pill) and risk-reduction counselling. In cases of IPV or sexual assault, youth will be referred for onward care. Referral pathways will be established to ensure prompt referral.

There is growing evidence from randomised clinical trials that use of oral daily PrEP confers significant protection against HIV acquisition, but it is currently unclear how the results of those trials will be incorporated into national guidelines.

New developments will be reviewed during the course of the trial. If the provision of PrEP is incorporated in local guidelines during the course of the trial, the intervention will be adapted appropriately.

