### **ii.5.5.2 Study Aim and Objectives**

This sub-study aims to assess current knowledge, attitudes and practices regarding STIs; to assess knowledge, attitudes and perceived barriers towards accessing STI testing and partner notification; and to determine factors predicting acceptance of STI testing. The uptake, yield and prevalence of STI testing will be assessed in the intervention arm. In addition, we will sample a proportion of participants in the endline survey to investigate the impact of offering unselected STI testing on the population level prevalence of STIs.

The objectives are:

1. To assess knowledge, attitudes and practices towards STIs
2. To assess attitudes towards accessing STI testing including site of testing and mechanisms of receiving results
3. To assess attitudes and perceived barriers to partner notification for STIs
4. To determine uptake, yield and prevalence of STI testing
5. To determine factors predicting acceptance of STI testing
6. To determine prevalence of STIs by study arm

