## • **7. Statistical considerations and Data analysis**

### **s. 7.1 Outcomes**

All outcomes will be measured in the cross-sectional survey after 2 years of implementation.

The primary endpoint is the proportion of HIV positive participants in the survey who have virological suppression (viral load <1000 copies/ml), by arm.

The secondary outcomes are

- Proportion of HIV positive participants who are aware of their HIV status
- Proportion of those aware of their HIV positive status who are taking ART
- Proportion of those on ART who are virally suppressed

These outcomes correspond to the individual UNAIDS 90-90-90 targets, while the primary endpoint is the product of all three.

Other outcomes will be measured among all survey participants, regardless of HIV status. They are

- Proportion with knowledge of their HIV status
- Proportion with STIs
- Proportion of males circumcised
- Proportion of females using modern methods of contraception
- Proportion with good MHM (defined as using a clean menstrual management material to absorb or collect blood that can be changed in privacy as often as necessary for the duration of the menstruation period, using soap and water for washing the body as required, and having access to facilities to dispose of used menstrual management materials)
- Proportion with symptoms of common mental disorders (measured using the Shona Symptom Questionnaire-14 with a cutpoint of 9)
- Proportions who report tobacco, alcohol and substance use
- Sexual behavior (including no. of sexual partners in the past year and condom use)

ART drug resistance will be measured in samples that are virologically non-suppressed (subject to funding).

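### The STI comparison estimates the effect of the whole CHIEDZA package, not of STI testing, and its outcome does not name the organisms that count

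*Combined protocol and SAP*

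**What the plan says.** **Aim.** Section 5.5.2 samples endline survey participants "to investigate the impact of offering unselected STI testing on the population level prevalence of STIs". The Executive Summary says the same: "to investigate the effect of providing unselected STI testing on prevalence of STIs". The formal objective 6 in 5.5.2 is more modest: "To determine prevalence of STIs by study arm". Outcome 6 in 5.5.4 matches it.

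**Contrast.** Section 2.3 randomises clusters to the community-based intervention or to "Control Arm - Existing HIV and SRH services". Table 1 and section 3.2.4 put condoms, risk-reduction counselling and syndromic STI management in the package alongside STI testing. The Executive Summary limits unselected STI testing, and the assessment of STI outcomes, to the 16 clusters in Harare and Bulawayo.

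**Outcome.** Section 7.1 lists "Proportion with STIs" among the other outcomes, below the primary and secondary ones, and does not define it further. Table 8 takes a control value of 17% without giving a source or an organism set.

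**Organisms.** Section 1.2 of the appendix (Eligibility for the survey) says that participants recruited on STICH days "were asked to provide a urine sample which will be tested for 5 STIs": *C. trachomatis*, *N. gonorrhoeae*, *T. vaginalis*, *U. urealyticum* and *M. genitalium*. Section 3.2.4 describes what the service does: "CHIEDZA will offer testing for GC and CT (male and female clients) and for TV (females only), contingent upon availability of test kits".

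**The concern.** There are two separate problems.

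**Attribution.** The aim asks a causal question about one component, but the randomised arms differ by all components. If STI prevalence is lower in the intervention clusters, the design cannot say whether testing, condoms, counselling or other parts of the package lowered it. A reader who takes the aim at its word would draw a conclusion that the comparison does not support.

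**Outcome definition.** Any of five organisms, any of three, or each organism separately are all compatible with section 7.1. Five results per person will be available, so an open definition leaves room to choose after the data are seen. It also leaves unclear which outcome Table 8 powers. If the analysed outcome included organisms that the service does not test for, and these did not respond, the risk ratio would move towards 1 and power would be lower than planned.

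**Working it through.** **1. What the arms differ by**

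| | Intervention, Harare and Bulawayo | Control, Harare and Bulawayo | Intervention, Mashonaland East |
|---|---|---|---|
| CHIEDZA package | yes | no | yes |
| Unselected STI testing | yes | no | no |
| STI outcome assessed | yes | yes | no |

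The first two columns differ in two rows at once. The third column would be the package without testing, but STIs are not measured there. Timing adds to the difficulty: the package runs for 30 months (section 2.3), while testing is planned for at least 12 months before the survey (section 5.5.3). Some of any difference could therefore have arisen before testing began.

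**2. Reproducing Table 8**

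Inputs from Table 8 are control prevalence p0 = 0.17, m = 300 per cluster, and coefficient of variation k = 0.25 or 0.30. The 16 clusters randomised 1:1 give 8 per arm. Two-sided 5% significance is assumed; it is not stated, but it fits the planned 95% confidence intervals.

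- V = p0(1−p0)/m + p1(1−p1)/m + k²(p0² + p1²)
- δ = (p0 − p1) × √(8/V)
- Power comes from the noncentral t distribution with 16 − 2 = 14 degrees of freedom and noncentrality δ.

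Solving for p1 gives 10.85%, 10.0%, 10.0% and 9.1%. The table states 11%, 10%, 10% and 9%, so it is sound for whatever outcome has a control prevalence of 17%. At 17% against 11% with k = 0.25, V = 0.00336, δ = 2.93 and power is 78%.

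**3. If all five organisms were pooled and 17% is the three-organism prevalence**

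Assume that the tested organisms fall from 17% to 11%, and that the untested two add an independent prevalence u that does not change. The pooled prevalence is 1 − (1 − p)(1 − u). The documents do not give u, so a range is shown at k = 0.25.

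| u | Control | Intervention | Risk ratio | δ | Power |
|---|---|---|---|---|---|
| 0 | 17.0% | 11.0% | 0.65 | 2.93 | 78% |
| 2% | 18.7% | 12.8% | 0.68 | 2.61 | 68% |
| 5% | 21.2% | 15.5% | 0.73 | 2.22 | 54% |
| 10% | 25.3% | 19.9% | 0.79 | 1.75 | 37% |

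Two changes of assumption matter:

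- If the between-cluster standard deviation stays at its three-organism value and does not grow with the pooled prevalence, power is about 75%, 71% and 64% at u = 2%, 5% and 10%.
- If the package lowers the untested organisms in the same ratio (0.11/0.17 = 0.65), the pooled risk ratio at u = 10% is [1 − 0.89 × (1 − 0.10 × 0.647)]/0.253 = 0.66, and power stays at about 77%.

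**4. If 17% already counts all five**

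Let a share s of the 17% be due only to untested organisms and stay unchanged. The intervention prevalence is then 0.17 × [s + (1 − s) × 0.647]. For s = 10%, 20% and 30% this is 11.6%, 12.2% and 12.8%, with power of about 68%, 56% and 45% at k = 0.25.

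The only related figure in the protocol is 3.5% mycoplasma infection in men with urethral discharge (section 5.5.1). That is a symptomatic clinic population and does not cover *Ureaplasma*, so it cannot fix u or s.

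**The case against.** **On attribution.** Objective 6 and outcome 6 ask only for prevalence by arm, and section 2.3 states the arms plainly. The causal wording appears in one sentence each of the Executive Summary and section 5.5.2. That is fair and makes the correction small, but those two sentences tell a reader what the comparison is for. Syndromic management should also not be leaned on as an arm difference: section 3.2.4 calls it the standard of care in many low- and middle-income countries, so control clusters may well have it. The point stands without it. A reader might infer that a favourable result will be reported as the effect of testing; the documents do not say so.

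**On the outcome.** A reader might infer that the outcome is any of five organisms and that the effect is therefore diluted. The documents do not support this. The five-organism list describes the assay in a passage on survey procedures and does not define an outcome, while section 5.5.1 speaks of screening for gonorrhoea, chlamydia and trichomonas. Dilution also requires that the untested organisms do not change. The service's testing does not detect them, but the contrast is the whole package, and condoms or counselling could lower them too. The direction and size of any net effect are therefore unknown.

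**On importance.** This is one of the other outcomes in section 7.1. It nonetheless has its own stated aim, its own sampling scheme and its own power table, so it deserves a defined outcome.

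**Conclusion.** Two points hold. First, the comparison estimates the CHIEDZA package including STI testing against existing services in Harare and Bulawayo; it cannot answer the question about testing alone that the Executive Summary and 5.5.2 pose. This follows from the design and needs no assumption. Second, the STI outcome and Table 8's 17% are not tied to any set of organisms, although the survey measures five and the service tests three in females and two in males.

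A loss of power is conditional. It occurs if all five organisms are pooled and the untested two do not respond. With 17% as the three-organism prevalence, independence and a coefficient of variation of 0.25, power goes from 78% to about 68%, 54% or 37% for an added 2%, 5% or 10%. It is almost unchanged if those organisms fall in the same ratio. If the outcome is restricted to the organisms behind the 17%, Table 8 stands. The wording should be corrected, but this is not a demonstrated flaw in the power calculation and does not touch the primary outcome.

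**What to change.** - **Executive Summary and 5.5.2:** restate the aim as the effect of the CHIEDZA package including STI testing, compared with existing services, in line with objective 6. Limit the conclusion to that.
- **7.1:** define the STI outcome as positive for *C. trachomatis*, *N. gonorrhoeae* or *T. vaginalis*. State whether *T. vaginalis* in males counts, since the service does not test males for it, and give results by sex. Report *M. genitalium* and *U. urealyticum* separately, as organisms that the service does not test for.
- **Table 8:** state which organisms the 17% refers to and its source. If it is not the set defined in 7.1, correct it and recompute the table.
- Settle the definition without reference to results by arm.

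The cost is a narrower conclusion and slightly more reporting. No new data are needed.

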### **iii.5.5.3 Sub-study methods**

#### ***Recruitment***

Youth attending the CHIEDZA service sites will be eligible. Those attending the CHIEDZA service who express an interest in enrolling in the sub-study will be given the opportunity to obtain more information and ask questions. In stage 1 (Harare only), purposive sampling will be used to deliberately select equal numbers of male and female clients who did and did not agree to STI testing. In stage 2, consecutive sampling will select clients for questionnaire administration. Inclusion criteria will be age 16 to 24 years inclusive, willingness to participate and the ability to provide signed informed consent. Exclusion criteria include an inability to communicate or read in English or Shona. Participation in the sub-study will be optional and it will be emphasized that care of those who decline to

participate will not be adversely affected. Following this, STI testing will continue to be offered in the intervention clusters (Harare and Bulawayo).

### ***Data Collection***

In Stage 1, consenting participants will provide basic sociodemographic information. They will then undergo a semi-structured interview, collecting qualitative data on the following domains:

- Knowledge of sexually transmitted infections
- Attitudes towards STI testing
- Current practices regarding STI testing and treatment-seeking behaviour
- Attitudes and perceived barriers to partner notification

Stage 2 will follow completion of stage 1. Consenting participants will undertake a structured questionnaire. The exact questions and available options for the questionnaire will be refined based on the responses to the semi-structured interviews from stage 1. The questions will fall into the following domains:

- Sexual history including history of previous STIs
- Knowledge of STIs
- Attitudes and practices towards STI testing
- Attitudes and perceived barriers to partner notification

### ***Qualitative methods***

Participants will be purposively selected as described above for stage 1 of the sub-study. Data collection by semi-structured interviews will be performed until data saturation is reached. Other qualitative studies assessing STI testing in young people noted data saturation following between seventeen and twenty-four interviews. Our study will likely have a similar data saturation point. The semi-structured interviews will use semi-structured topic guides based on the domains noted above. They will be conducted in English or Shona, depending on the participants' preference. Written informed consent will be obtained from each participant before the interview. Interviews will be digitally recorded, and written notes will be taken. Each interview is expected to take between 30 minutes and 1 hour. Audio recordings of the interviews will then be transcribed verbatim and then translated (if applicable) into English for analysis. Thematic analysis will be performed to provide a qualitative summary of knowledge, attitudes and practices as follows: familiarisation with the data; generating initial codes; searching for themes; reviewing potential themes; defining and naming themes; and producing the report.

